### Study procedures

#### Baseline questionnaire

All included patients are interviewed according to a study-specific questionnaire regarding presenting symptoms as well as occurrence and intensity of chest pain and/or breathing difficulties.

#### Echocardiography

The echocardiographic screening protocol has been presented above (study design overview, cardiac screening). All echocardiographic views obtained are saved in the patient’s medical chart, and echocardiographic data according to standard clinical protocol are registered for study purposes. For patients with positive screening results, or where secondary incidental findings emerge, the need for further cardiac investigation/intervention will be assessed in collaboration with the cardiology department.

#### ECG and chest X-ray

Examinations with ECG and chest X-ray are performed in hospital the same day/days as echocardiography. These procedures are performed in accordance with clinical routine.

#### Blood samples

Outside of clinical routine, blood sampling for analysis of NT-proBNP is performed in hospital on the same day/days as echocardiography. If separate specific IC is signed, blood sampling for biobanking will also be obtained at day 0 for metabolomics, proteomics, microRNA and messenger RNA analyses. When available, baseline laboratory work-up from clinical routine is collected regarding troponin I, NT-proBNP, creatinine, haemoglobin, white cell count, C-reactive protein (CRP), electrolytes (sodium, potassium, calcium) and venous/arterial blood gases.

#### Killip classification

Killip class will be assessed using the contemporary Killip classification (table 1), incorporating clinical findings together with chest imaging.^20 21^ Pulmonary ultrasound will be used to assess the presence of interstitial fluid in a subset of patients where Killip class is uncertain and needs further confirmation.

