### Objectives and outcomes

#### Primary objectives

To determine the incidence of reversible left ventricular systolic dysfunction (as a proxy for Takotsubo stunning) in patients hospitalised for AECOPD at Sahlgrenska University Hospital (Gothenburg, Sweden).To investigate in-hospital clinical manifestations of AHF (defined as Killip class >1, table 1) in patients with signs of Takotsubo stunning versus those without, among patients hospitalised for AECOPD at Sahlgrenska University Hospital.

**Table 1 T1:** Killip classification of acute left-sided heart failure, based on clinical signs supported by chest imaging

Killip class I	No clinical/radiological signs of heart failure.
Killip class II	Clinical and radiological signs of heart failure but not pulmonary oedema (distinct bilateral rales or crackles over lungs suggesting interstitial fluid supported by interstitial fluid on chest X-ray*).
Killip class III	Clinical picture of frank pulmonary oedema supported by radiological* signs.
Killip class IV	Cardiogenic shock or hypotension (measured as systolic blood pressure lower than 90 mm Hg) and evidence of peripheral vasoconstriction (oliguria, cyanosis or sweating).

* Pulmonary ultrasound may be used to confirm Killip class.

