### Outcomes

#### Primary outcomes

Cumulative incidence of reversible RWMA or reversible left ventricular systolic dysfunction (as proxy for Takotsubo stunning) according to screening and follow-up echocardiography.Clinical signs of AHF during hospitalisation (defined as Killip class >1, table 1, components of classification documented in hospital medical chart).

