### Patient and public involvement

This study originates from the person-centred care context at Sahlgrenska University Hospital, where patient perspectives are a central part of everyday clinical work, in accordance with the hospital’s core value explicitly phrased in the hospital policy: ‘For the patient, with the patient’. Through ongoing dialogue with patients, previously unrecognised clinical needs and gaps in existing knowledge were identified, which influenced the study objectives. This is particularly relevant since the majority of investigators and collaborators in this study are also treating physicians for the included patients. Patients and the public were not otherwise involved in the study design or conduct.

Results of the study will be disseminated through scientific publications and presentations. In addition, findings will be communicated in formats accessible to patients and the public, including plain language summaries and dissemination through relevant clinical settings where patients receive care.

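### Nothing in the plan keeps the Killip rating behind the primary heart-failure outcome independent of the screening echocardiogram

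*Protocol article*

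**What the plan says.** **Outcome.** Under Primary outcomes, AHF is Killip class above I during the hospital stay, with "components of classification documented in hospital medical chart". The Killip classification section describes the rating as "incorporating clinical findings together with chest imaging". In Table 1, class II needs both clinical and radiological signs, and class III needs a picture of pulmonary oedema with radiological support. Class IV is shock, or low systolic pressure with signs of vasoconstriction.

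**Lung ultrasound.** The Killip classification section says "Pulmonary ultrasound will be used to assess the presence of interstitial fluid in a subset of patients where Killip class is uncertain"; the footnote to Table 1 says "Pulmonary ultrasound may be used to confirm Killip class". Neither place defines an uncertain class or sets the timing of the ultrasound relative to the echo.

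**Exposure.** The Statistical plan relates a positive screening result to AHF. The Echocardiography section says "All echocardiographic views obtained are saved in the patient’s medical chart", and that for positive screens "the need for further cardiac investigation/intervention will be assessed in collaboration with the cardiology department". The Cardiac screening section adds clinical work-up of any dysfunction found. Chest X-ray is done on the same day as the echo (ECG and chest X-ray).

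**People.** Under Patient and public involvement: "the majority of investigators and collaborators in this study are also treating physicians for the included patients".

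No section says who assigns the Killip class, when, or with what information.

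**The concern.** In a comparison of AHF between screen-positive and screen-negative patients, the outcome should be determined without knowledge of the exposure. Killip II turns partly on judgement: crackles thought to suggest interstitial fluid, supported by a film reading. The article itself says, in the Abstract and under Scientific and clinical importance, that symptoms of AHF and of the exacerbation overlap and that one can mask the other. Equivocal patients are therefore to be expected. An equivocal patient known to have an impaired ventricle may be called Killip II, while the same findings with a normal echo may be put down to the lung disease.

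The undefined ultrasound trigger adds a second opening, because how uncertain a clinician feels can depend on the echo. Misclassification of this kind differs between the groups by construction. Adjustment for age, sex or other baseline confounders does not correct it.

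**Working it through.** **1. Can the echo result reach the rating?** There are two possible routes.
- *Investigators rate.* Most of them treat the patients, and positive screens are worked up clinically with cardiology, so the result is available to them.
- *The class is abstracted from the chart.* Signs charted and imaging ordered after screening come from a care team that could see the result, and the chart itself contains the echo.

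On neither route does the text mask the rater, place the rating before the echo, or restrict which findings count. The outcome covers the whole stay, so post-echo findings count.

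**2. The plan's own sample size.** Inputs from Statistical plan and sample size: 150 patients, 1:10 ratio, AHF 30% v 5%, α = 0.05 (two-sided assumed).
- n₁ = 150/11 = 13.64 and n₂ = 136.36.
- Pooled proportion p̄ = (0.30 + 10 × 0.05)/11 = 0.0727.
- Power = Φ{[0.25 − 1.96·√(p̄(1−p̄)(1/n₁ + 1/n₂))] / √(0.30·0.70/n₁ + 0.05·0.95/n₂)} = Φ{(0.25 − 0.1446)/0.1255} = Φ(0.840) = 79.96%.

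The stated 80% is reproduced, so the arithmetic is not at fault.

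**3. How few patients carry the contrast.** With about 14 positives, 30% is 14 × 0.30 = 4.2 patients and 5% is 14 × 0.05 = 0.7. One reclassified positive moves the group's rate by 1/14 = 7 percentage points.

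**4. Illustration of the bias.** Assume the true AHF rate p₀ is equal in both groups, and that a share u of truly Killip I positives is upgraded, with no upgrading among negatives. The documents give no value for u, so a range is shown. The apparent rate in positives is p₁ = p₀ + (1 − p₀)u. The false-positive rate is the exact probability of p ≤ 0.05, summed over all possible 14 v 136 tables.

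| p₀ | u | p₁ | Apparent OR | Fisher | Chi-square |
|---|---|---|---|---|---|
| 5% | 0 | 5.0% | 1.0 | 2% | 5% |
| 5% | 5% | 9.8% | 2.0 | 10% | 17% |
| 5% | 10% | 14.5% | 3.2 | 24% | 34% |
| 5% | 20% | 24.0% | 6.0 | 56% | 67% |
| 10% | 0 | 10.0% | 1.0 | 2% | 4% |
| 10% | 10% | 19.0% | 2.1 | 17% | 22% |
| 10% | 20% | 28.0% | 3.5 | 43% | 50% |

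At p₀ = 5%, u of about 26% gives 0.05 + 0.95 × 0.263 = 0.30, which is the whole planned contrast with no true difference.

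**5. The same in counts.** Against 7/136 negatives (136 × 0.05 = 6.8), Fisher p is 0.552 for 1/14 positives, 0.199 for 2/14, 0.053 for 3/14 and 0.011 for 4/14. Moving from 1 to 4 means upgrading 3 of 13 Killip I positives (23%) and no negatives. This is one scenario only.

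**The case against.** A reader might infer that the treating physicians assign the Killip class with the echo in front of them. The documents do not support that. The sentence on treating physicians stands in a patient-involvement paragraph and does not mention outcome rating. Storing the echo in the chart does not show that the rater opens it. A condensed article may also leave masking and adjudication to a full protocol that is not at hand.

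Killip is also less subjective here than it may look. Crackles alone do not make class II, because classes II and III need radiological support. Findings recorded before the echo cannot be influenced by it, and inclusion may be up to 72 hours after admission. Ultrasound can lower an uncertain class as well as raise it. The upgrade shares are assumed, and the planned test is multivariable logistic regression rather than Fisher's test.

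All of this stands as a limit on certainty and size. It does not dispose of the point. The text positively describes a shared chart, clinical action on positive screens, mostly treating investigators and an undefined ultrasound trigger. The film is taken on the same day as the echo, and nothing masks its reader. A masked adjudicator in an unseen document would reduce the problem, but the source notes and the choice to do ultrasound would still be open to the echo result.

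**Conclusion.** The point holds as a risk of bias: as written, the plan does not keep the primary AHF outcome independent of the exposure. The documents do not show that any rater sees the echo, nor that a difference, if found, would be an artefact.

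The size is unknown because no misclassification rate is given. The calculations show fragility. With about 14 positives, upgrading an assumed 5% to 20% of those truly in Killip I takes the Fisher false-positive rate from 2% to between 10% and 56% at a true rate of 5% in both groups. This rests on upgrading in positives only. Two-way errors, or errors in both groups, would give less.

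The repeat day-1 chest X-ray that Table 2 schedules only for screen-positives is a separate source of unequal ascertainment. The rating problem would remain with identical tests in both groups. The change should be made now, with 56 of 150 patients enrolled and 150 − 56 = 94 still to come.

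**What to change.** In the Killip classification and Primary outcomes sections, state that:

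1. The Killip class for the primary outcome is assigned by an existing study-team member who is not treating that patient. The rater works from an extract of recorded signs, vital signs and chest X-ray, with echo and NT-proBNP withheld. A scheduled day-1 film in the extract would itself reveal a positive screen, so the extract should have the same content in both groups.
2. Lung ultrasound done after the echo result is known is left out of the primary rating. No echo result is delayed for this purpose, and clinical use of ultrasound is unaffected.
3. A sensitivity analysis uses only Killip findings recorded before the echo result.
4. Patients already enrolled are re-rated from masked extracts of the chart components already documented.

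The cost is protocol wording and abstraction time for about 150 patients, with no new visits, tests or staff. Two limits remain. Notes written after the echo may still hint at its result, and the sensitivity analysis gives up later findings from an outcome defined over the whole stay.

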### Collection of data

After IC, data as declared below are collected (also summarised in table 2, schedule of events). If investigations have been performed after contact with healthcare but before IC (ie, after arrival of ambulance/arrival to emergency department/hospital ward but before IC), these data may be included as study data provided that the IC is signed, to avoid unnecessary repeats of investigations/procedures.

**Table 2 T2:** Schedule of events

Schedule of events	Admission	Inclusion (day 0) (within 72 hours of admission)	Day 1 24±6 hours*	Day 2 48±12 hours*	Day 3 72±12 hours*	In hospital (including date)	Postdischarge within 6 months
Eligibility criteria and informed consent		X					
Time from admission to inclusion		X					
GOLD grade (1–4) and group (A, B, E)		X					X
Severity of COPD exacerbation (mild, moderate, severe)^18^		X					
Baseline characteristics including baseline medication	X	X					
Blood pressure and heart rate	X	X	X	X	X		X
Pulse oximetry and respiratory rate	X	X	X	X	X		X
Body temperature	X	X	X	X	X		
Blood work-up (clinical routine)	X†	X†					X
Symptom questionnaire		X					
Echocardiography (standard clinical protocol)		X	(X)‡				(X)‡ day 30 (±48 hours)
NT-proBNP	X†	X	(X)‡				
Biobank (if separate consent)		X					
12-lead ECG	X†	X	(X)‡				
Chest X-ray	X†	X	(X)‡				
Exacerbation-specific treatment	X	X	X	X	X		
Complications and outcome	X	X	X	X	X	X	X
Spirometry, diffusion capacity, body plethysmography							X
6-minute walk test. COPD assessment test, mMRC							X

* After inclusion.

† When available.

‡ Only if positive in screening.

COPD, chronic obstructive pulmonary disease; GOLD, Global Initiative for Obstructive Lung Disease; mMRC, modified Medical Research Council Dyspnea Scale; NT-proBNP, N-terminal pro-B-type natriuretic peptide.

#### Baseline characteristics

Baseline characteristics include age, sex, body mass index, comorbidities, smoking status, baseline medication, presenting symptoms and signs, and are collected from interview with the patient and/or the patient’s medical chart. The time from admission (defined as arrival to hospital, either to emergency department or directly to hospital ward if bypassing emergency department) to inclusion is registered for all patients.

#### COPD characteristics

For all patients, COPD severity stage by GOLD criteria will be registered based on previous clinical records when available, and severity of exacerbation will be defined and registered according to the Rome criteria as suggested by GOLD.^17 22^ The patients’ COPD will be characterised at the time of inclusion and will then be further characterised in a stable state within 6 months after discharge. Specifically for classification of severity of AECOPD, the following variables are used: dyspnoea visual analogue scale from symptom questionnaire, respiratory rate, heart rate, oxygen saturation, CRP and arterial blood gas (table 3).^22^

**Table 3 T3:** Severity of AECOPD

Mild (default)	Dyspnoea VAS <5. RR <24 breaths per minute. HR <95 beats per minute. Resting oxygen saturation ≥92% breathing ambient air (or patient’s usual oxygen prescription) AND change ≤3% (when known). CRP <10 mg/L (if obtained).
Moderate (meets at least three of five)	Dyspnoea VAS ≥5. RR ≥24 breaths per minute. HR ≥95 beats per minute. Resting oxygen saturation <92% breathing ambient air (or patient’s usual oxygen prescription) AND/OR change >3% (when known). CRP ≥10 mg/L. If obtained, arterial blood gas may show hypoxaemia (PaO_2_ ≤8.0 kPa) and/or hypercapnia (PaCO_2_ >6.0 kPa) but no acidosis (pH >7.35).
Severe	Arterial blood gas shows hypercapnia and acidosis (PaCO_2_ >6.0 kPa and pH <7.35).

Adapted from Celli *et al*^22^ (The Rome Proposal).

AECOPD, acute exacerbation of chronic obstructive pulmonary disease; CRP, C-reactive protein; HR, heart rate; RR, respiratory rate; VAS, visual analogue scale.

Also, the following COPD/exacerbation-specific characteristics (when available as part of clinical routine) are collected at the time of hospitalisation: chest CT, nasopharyngeal swabs for detection of viral infection, sputum sampling for culture, handheld spirometry for forced expiratory volume in 1 s, COPD assessment test, level of oxygen supply (baseline home oxygen and/or oxygen administered because of hypoxia during exacerbation) and treatment choices (inhalations, antibiotics, corticosteroids).

#### In-hospital follow-up

Blood pressure, heart rate, pulse oximetry, respiratory rate, body temperature and AECOPD-specific treatments (including detailed information on beta-2 agonist inhalation and other inhalation treatment) are registered daily until day 3 after inclusion. Complications (including date and approximate time) during hospitalisation are collected consecutively for all patients according to the following: acute respiratory failure/deterioration, AHF/cardiac decompensation, acute myocardial infarction, stroke, PE, peripheral embolisation, admission to intensive care unit, need for respiratory support, in-hospital cardiac arrest and in-hospital death.

#### Postdischarge follow-up

Echocardiography at day 30 (±48 hours) is performed after discharge or in hospital depending on length of stay (only screening-positive patients). In the stable state, the following characteristics from re-evaluation (as part of clinical routine after hospital care for AECOPD, according to hospital medical chart) are collected: postbronchodilator spirometry, diffusion capacity, static lung volumes (body plethysmography), 6-minute walk test, COPD assessment test, modified Medical Research Council Dyspnea Scale, oxygen saturation and/or blood gases and GOLD A, B, E classification. Also, all-cause and cardiovascular mortality within 1 year after inclusion will be registered (data from Swedish Cause of Death Register, National Board of Health and Welfare).

### Outcomes

#### Primary outcomes

Cumulative incidence of reversible RWMA or reversible left ventricular systolic dysfunction (as proxy for Takotsubo stunning) according to screening and follow-up echocardiography.Clinical signs of AHF during hospitalisation (defined as Killip class >1, table 1, components of classification documented in hospital medical chart).

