### Study design overview

CATCH is a prospective observational cohort study of patients admitted to Sahlgrenska University Hospital for AECOPD. COPD is defined as a documented physician diagnosis of COPD in the hospital or primary care medical record. AECOPD is defined according to the 2024 Global Initiative for Obstructive Lung Disease (GOLD) report as: increased dyspnoea and/or cough and sputum that worsens in <14 days which may be accompanied by tachypnoea and/or tachycardia and is often associated with increased local and systemic inflammation caused by infection, pollution or other insult to the airways.^17 18^ Patients meeting all inclusion criteria and no exclusion criteria are eligible for inclusion and screening for echocardiographic signs of regional wall motion abnormality (RWMA) and/or left ventricular systolic dysfunction. Inclusion takes place from Monday to Friday, and each patient can be included only once; repeat admissions for AECOPD will not lead to reinclusion.

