### Study population and eligibility criteria

#### Inclusion criteria

Adult patients (≥18 years old) admitted to a hospital ward for AECOPD.Inclusion within 72 hours of admission.Written informed consent (IC).

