**Figure 1 F1:**
[figure not shown]
Screening algorithm. CATCH, Cardiac Assessment and Takotsubo-stunning among COPD-exacerbations in-Hospital; COPD, chronic obstructive pulmonary disease; RWMA, regional wall motion abnormality.

Negative=absence of RWMA and no left ventricular systolic dysfunction (LVEF ≥50%).

For patients with a positive screening result, echocardiography will be repeated after 24 (±6) hours and at 30 days (±48 hours). Within the screening-positive group, patients who demonstrate reversibility on repeat echocardiography will constitute the CATCH case group (Takotsubo stunning group), provided that no alternative cause of transient cardiac dysfunction has been identified (according to diagnostic criteria for Takotsubo^16 19^). Reversibility will be defined as normalisation or significant improvement in left ventricular systolic function, indicated by resolution of left ventricular akinesia/hypokinesia and/or improved LVEF ≥10 percentage points.

Cardiac dysfunction detected through study screening will be investigated based on clinical findings and symptoms as per clinical routine, to address alternative causes to Takotsubo stunning. For patients with ongoing or easily provoked chest pain, timely coronary angiography is mandatory to exclude coronary artery occlusion. To exclude or confirm other causes, such as myocarditis or chronic coronary syndromes, cardiac MRI or myocardial perfusion scintigraphy, respectively, may be used according to clinical routine. Hence, in cases with reversible left ventricular dysfunction, Takotsubo stunning will be validated based on clinical investigation together with diagnostic criteria for TS.^19^

If patients within the screening-positive group do not display reversibility by day 30±48 hours (or through further assessment during clinical routine follow-up within 6 months, figure 1), the RWMA and/or left ventricular systolic dysfunction will be considered persistent (ie, fulfilling exclusion criteria unknown at time of inclusion) and the patient will be excluded from analysis.

Patients who turn out negative in screening will constitute the CATCH control group.

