### Statistical plan and sample size

Inclusion is planned over approximately 3 years to estimate the cumulative incidence of Takotsubo stunning in patients hospitalised for AECOPD. The primary analysis will assess the association between a positive screening result and clinical manifestations of AHF using multivariable logistic regression. The model will adjust for relevant baseline confounders, with a significance threshold of α=0.05.

For the primary analysis, the required sample size is estimated at 150 patients, assuming a 1:10 ratio of positive to negative screening results. In previous research randomly investigating the correlation between clinical and echocardiographic signs of heart failure, clinical heart failure was present in approximately 50% of patients with echocardiographic left ventricular systolic dysfunction (LVEF <40%).^23^ Given the higher cut-off for systolic dysfunction in CATCH (LVEF <50%) and inclusion of newly detected RWMA as positive screening (ie, also in absence of reduced LVEF), together with the exclusion of patients with prior type 1 myocardial infarction or known persistent systolic dysfunction, we conservatively estimate the proportion of clinical heart failure in the positive screening group to approximately 30%. Accordingly, our sample provides 80% power to detect a difference in the incidence of clinical signs of AHF between the groups, assuming 30% in the positive screening group and 5% in the negative screening group with α=0.05.

Secondary and tertiary outcomes will be analysed using linear regression for continuous outcomes and logistic regression for dichotomous outcomes, in both unadjusted and adjusted models. A Cox proportional hazards model adjusted for baseline confounders will be applied to analyse 1-year mortality. These analyses are considered explanatory or hypothesis generating. Results will be reported as effect estimates with 95% CIs and unadjusted p values, with false discovery rate correction applied to account for multiple comparisons.^24^

Unadjusted and adjusted analyses (including covariates age and sex) will be presented as separate models. A sample size of 150 patients, with an assumed 1:10 ratio of positive to negative screening results, translates to a total number of 15 events. Given the relatively low number of expected events, all further adjustment will include only clinically meaningful covariates and will be presented as separate models.

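### Primary outcome 1 is called a cumulative incidence, but cases can be found only at one screening echo at a variable time within 72 h of admission, so it measures the proportion with later-reversible dysfunction detected at screening

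*Protocol article*

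**What the plan says.** The Primary outcomes section names the first outcome "Cumulative incidence of reversible RWMA or reversible left ventricular systolic dysfunction", as a proxy for Takotsubo stunning, judged from screening and follow-up echocardiography. Statistical plan and sample size says that the inclusion period serves "to estimate the cumulative incidence of Takotsubo stunning in patients hospitalised for AECOPD".

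Case finding works as follows:

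- Inclusion criteria: "Inclusion within 72 hours of admission". Table 2 schedules the screening echo at inclusion (day 0).
- Study design overview: "Inclusion takes place from Monday to Friday", which widens the spread of screening times.
- Cardiac screening and the Table 2 footnote: echo at 24 h and at 30 days is scheduled only after a positive screen. These examinations decide reversibility.
- Cardiac screening: "Patients who turn out negative in screening will constitute the CATCH control group". No second echo is scheduled for them.
- Cardiac screening: positives whose dysfunction persists are removed from the analysis.

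The Introduction describes the syndrome as quick to start and, in most cases, fully recovered after days to weeks. Under Baseline characteristics, the interval from arrival "to inclusion is registered for all patients". Under In-hospital follow-up, complications, including AHF, are collected with date and approximate time.

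**The concern.** A cumulative incidence counts everyone who develops the condition over a stated period. Here the period is not stated, and only one examination per patient can reveal a case. An episode that ended before that examination, or started after it, leaves no trace in the outcome.

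The protocol's own rationale makes both routes plausible. Recovery can take only days. The section on scientific importance also names beta-2 agonists, part of the treatment of the exacerbation, as a likely trigger, so onset after admission is possible.

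Two things are at stake. The headline figure would be quoted as an incidence although it depends partly on how soon after arrival patients were screened. Missed episodes also sit among the controls, which weakens the contrast in the second primary outcome when it is read as stunning versus no stunning. In addition, AHF is counted over the whole hospital stay while group membership may be set up to 72 h into it, so some AHF may have been documented before the echo.

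**Working it through.** **1. The plan's own figure.** No target or precision is given for primary outcome 1. The only calculation is 150 patients for 80% power on AHF (Statistical plan and sample size: 30% versus 5%, ratio 1:10, α = 0.05; two-sided assumed).

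- Group sizes: 150/11 = 13.64 and 136.36.
- Pooled rate: (13.64 × 0.30 + 136.36 × 0.05)/150 = 10.91/150 = 0.0727.
- Standard error under the null: √[0.0727 × 0.9273 × (1/13.64 + 1/136.36)] = 0.0738.
- Standard error under the alternative: √[0.30 × 0.70/13.64 + 0.05 × 0.95/136.36] = 0.1255.
- z = (0.25 − 1.96 × 0.0738)/0.1255 = 0.84, so power is 0.80. The figure reproduces.

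**2. What one look can see.** Let T be onset, D duration and S the time of the screening echo, in hours from admission. An episode is seen only if T ≤ S < T + D. Timing can therefore remove episodes from the count but cannot add any.

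**3. How much might be missed.** The documents give no distribution for T or S, and only days to weeks for D. Assume S is uniform over 0–72 h.

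With fixed durations:

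| Assumed onset | Duration | Captured |
|---|---|---|
| At admission | 48 h | 48/72 = 67% |
| At admission | 72 h or more | 100% |
| Uniform over the 72 h before admission | 48 h | 48²/(2 × 72²) = 22% |
| Uniform over the 72 h before admission | 72 h | 50% |
| Uniform over the 72 h before admission | 7 days or more | 100% |
| Uniform over 0–72 h after admission | 72 h or more | 50% (the rest start after the echo) |

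With exponential durations and onset uniform over the 48 h before admission, take a mean of 5 days (120 h):

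- Share still present at admission: (120/48)(1 − e^−0.4) = 0.824.
- Share of those still present at the echo: (120/72)(1 − e^−0.6) = 0.752.
- Captured: 0.824 × 0.752 = 62% of all episodes, or 75% of those present at admission.
- By echo time: 0.824 × (120/24)(1 − e^−0.2) = 75% at 0–24 h, and 75% × e^−0.4 = 50% at 48–72 h.

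For means of 2, 5, 10 and 21 days, capture is 33, 62, 78 and 89% of all episodes, or 52, 75, 86 and 93% of those present at admission. If onset continues to 72 h after admission, it is 32, 50, 59 and 64%, or 38, 53, 61 and 65% once episodes that ended before admission are left out.

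**4. Consequence for both primary outcomes.** Let c be the captured share (assumed, 50–100%). Hold screening positives at 1/11 = 9.1% and treat all of them as stunning. Assume 30% AHF in missed cases and 5% in unaffected patients.

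- True proportion = 9.1%/c.
- Missed cases = 13.64/c − 13.64.
- f = missed/136.36.
- Control AHF = (1 − f) × 5% + f × 30%.

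| c | True proportion | Missed among controls | Control AHF | Power |
|---|---|---|---|---|
| 100% | 9.1% | 0 | 5.0% | 80% |
| 90% | 10.1% | 1.5 | 5.3% | 79% |
| 80% | 11.4% | 3.4 | 5.6% | 77% |
| 70% | 13.0% | 5.8 | 6.1% | 75% |
| 50% | 18.2% | 13.6 | 7.5% | 69% |

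If 9.1% is instead taken as the true proportion, there are fewer positives as well, and power at 90, 80, 70 and 50% capture is 77, 73, 69 and 59%. The plan states its ratio for screening results, so the table follows its wording.

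**5. A push the other way.** Removing persistent positives shrinks the denominator. For example, 10/150 = 6.7% becomes 10/145 = 6.9% if five are removed.

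**6. Precision by time band.** About 14 positives and 150 patients over three equal bands is roughly 5 of 50 per band, with an exact 95% interval of about 3% to 22%.

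**The case against.** The strongest reply is that the outcome does not rest on one echo alone. A case must also show reversibility at follow-up, known chronic dysfunction and prior type 1 infarction are excluded, and persistent dysfunction is removed. What is counted is therefore probably recent, transient dysfunction around the index exacerbation. This stands, and it means that plain point prevalence would be too crude a label. It does not recover episodes that the screening echo missed.

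Second, the loss may be small. If onset comes with the exacerbation before arrival and recovery takes a week or more, the fixed-duration model captures every episode. This also stands; the capture percentages above are illustrations, not estimates.

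Third, the plan states its 5% for screening-negative patients, so read literally it already includes any missed cases, and the planned power is then unaffected. The dilution matters when the result is read as stunning versus no stunning, as the second primary objective puts it.

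Three stronger readings are tempting and are not supported:

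- A reader might infer that the reported figure is a strict lower bound on incidence. Timing bias is downward, but the shrinking denominator pushes slightly up and the outcome is only a proxy, so the net direction is not proven.
- A reader might infer that time to inclusion will go unused. The article is condensed, its analysis plan is not shown, and its adjustment for baseline confounders does not rule the variable out.
- A reader might infer that AHF documented before the echo is misattributed. The echo may detect a state that had already caused it.

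**Conclusion.** The point holds as a mislabelled primary estimand. As designed, primary outcome 1 is the proportion of analysed patients with later-reversible dysfunction detected at a screening echo within 72 h of admission. It is not a cumulative incidence over the admission. This follows from the text and needs no assumption.

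The direction of the timing bias, zero or downward, follows from there being one look with no scheduled re-examination of negatives. Its size cannot be settled from the documents, because it depends on onset, duration and screening times that they do not give.

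The effect on the AHF comparison is modest for capture of 70% or more (power 75% to 80%) and becomes material only at low capture (69% at 50%), under the assumptions that missed cases have 30% AHF and that the 5% applies to unaffected patients. The sample size calculation itself is not in error on this account.

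**What to change.** 1. In Primary outcomes and in Statistical plan and sample size, restate the outcome as *proportion with reversible RWMA or left ventricular systolic dysfunction detected at a screening echo within 72 h of admission*. Align the wording of the first primary objective.
2. State that screening-negative patients are not re-examined and that bias from timing is downward. Do not call the figure a lower bound.
3. Report the proportion descriptively by time from admission to echo (0–24, 24–48, 48–72 h) with exact confidence intervals, and say in advance that they will be wide. Time to inclusion is already recorded. Where an echo done before consent is used, take the time of that echo.
4. Using the complication dates already collected, report how many AHF events were documented before the screening echo.

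Adding time to echo as a covariate in the AHF model is not a substitute, because it does not move missed cases out of the control group. The plan's assumptions also imply only about 11 AHF events (4.1 + 6.8), which leaves little room for more covariates.

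The cost is a wording change and two descriptive tables from data already collected, with no extra echocardiograms. It can be made now: 56 of 150 patients were enrolled at the stated status date, and analysis follows the end of inclusion. The downside is a more modest claim than incidence.
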